**Study question**

Is the STST a valid tool to measure functional exercise capacity; do STST performance correlates with the distance walked during the 6MWT in children and adolescents with CF?

**RESEARCH OBJECTIVES**

**General objectives**

To assess the validity of the STST to measure functional exercise capacity in children and adolescents with CF; and to address the associations between STST performance and other meaningful outcomes (respiratory and peripheral muscle strength, health-related quality of life, cardio-respiratory responses during both tests).

**Specifical objectives**

Main objective:

Assess the correlation between the STST performance and the distance walked during the 6MWT

Secondary objectives:

- Address the correlations between STST and 6MWT performances and the cardio-respiratory responses during both tests (heart rate HR; respiratory rate RR; pulsed oxygen saturation SpO2; blood pressure BP; dyspnea and leg fatigue)
- Address the correlations between both tests’ performances and; pulmonary function (forced vital capacity FVC; forced expiratory volume in 1s FEV1; peak expiratory flow PEF), respiratory muscle strength (maximal inspiratory and expiratory pressures MIP and MEP), quadriceps strength (QS) and health-related quality of life (HRQOL)
- Address the correlations between both tests’ performances and; anthropometric data (age, height, weight, body mass index BMI), hospitalizations and exacerbations within last year
- Question the specific insights of the STST in young children (from 6 to 10 years of age)
- Compare the cardio-respiratory responses between both similar tests (HR, RR, SpO2, BP, dyspnea and leg fatigue)
- Compare the cardio-respiratory responses between both different tests (HR, RR, SpO2, BP, dyspnea and leg fatigue)

**Data collection**

At the arrival of the subjects, investigators will collect:

- Age
- Gender
- Weight
- Height
- BMI
- Medical treatments
- Number of hospitalizations last year
- Number of exacerbations last year
- Lung function (FEV1, FVC, FEV1/FVC, PEF)
- Respiratory muscle strength (MIP and MEP°
- QS
- HRQOL
- Subjects signed consent

During the study procedure, investigators will collect:

- STST performances
- Distance walked during the 6MWT
- 6MWWork (Distance * weight)
- HR
- RR
- SpO2
- BP
- Dyspnea
- Leg fatigue

**STUDY HYPOTHESIS**

Investigators hypothesize that the STST is a valid tool and that STST performance will correlate with the distance walked during the 6MWT in children and adolescents with CF

**VALIITY OF THE STUDY**

External validity:

The aim of this study is to address the validity of the STST. This study also aims to compare cardio-respiratory responses during the STST and the 6MWT and to evaluate the associations between the STST and clinically important outcomes.

If the STST is valid, its use could be generalized in exercise testing for children and adolescents with CF. Moreover, this test could induce lower cardio-respiratory adaptations, dyspnea and fatigue and could easily be used in young children with CF. This test could be a reasonable option for addressing functional exercise capacity in young individuals with CF.

Further research could therefore be conducted to assess the precise repeatability of the STST as well as its responsiveness through the MCID (Minimal Clinically Important Difference).

Internal validity:

Selection bias: The same inclusion criteria will apply in the different CF Centers. All the subjects included will be free from exacerbation for at least 4 weeks to be included. This will be defined as the absence of a hospitalization or an intravenous antibiotic cure for at least 4 weeks [1]. All the analyses will be conducted on a single homogenous population of children and adolescents with CF.

Observation bias: All the procedures of the study will be similar in each of the CF Center. Field tests will be conducted according to the latest American Thoracic Society (ATS) and European Respiratory Society (ERS) guidelines [2]. The same rest period between each tests of 30 minutes will apply in each CF Centers [2]. This will minimize the effects of each testing procedures on the others. In order to account for the learning effect described for both 6MWT and STST, each test will be conducted twice [2, 3]. Standardized verbal information will be provided before the 6MWT in each of the CF Centers [2]. Although there is no mention of standardized information for the STST in the literature, we aimed to standardized the explanations before the test in all the Centers (see below). All the tests will be conducted within the same day. Subjects should not have had eaten 2 hours before the tests. The order of the tests will be randomized.

Confusion bias: This study is a randomized cross-over trial. Both tests will be conducted with the same subjects. In order to minimize the variation between subjects, 1 or 2 investigators maximum will conduct the tests in each center. The results of the first STST and 6MWT will not be communicated to the subjects before the second row to avoid any external influence.

**STUDY POPULATION**

**Inclusion criteria:**

- Subjects with CF;
- Aged 6 to 18 years;
- Male of female;
- Signed informed consent by the children and their parents, 24-hour pre-inclusion delay;
- Routinely assessed in Le Havre, Rouen or Caen CF Center
- Clinically stable (no exacerbation for at least 4 weeks)

**Non-inclusion criteria:**

- Contra-indications to exercise testing;
- Musculoskeletal or neurological disorders avoiding the realization of the field tests (fracture, sprain, peripheral or central nervous disease…);
- Other respiratory restrictive (scoliosis …) or obstructive (asthma…) disease;
- Other disease avoiding the realization of the tests;
- Unability to understand the study procedures;
- Symptoms of beginning exacerbation (fever, mucus plugging …)

**Exclusion criteria:**

- Unability to complete the study procedure
- Appearance of a non-inclusion criteria

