**Sample size estimation**

The sample size estimation showed that 36 participants were necessary to detect a correlation coefficient of 0.45 between the STST and 6MWT performances, with 80% power and an alpha level of 0.05. The final sample size aimed for was 40 since it was estimated that there would be an attrition rate of approximately 10%, based on experience in using these clinical tests with children: the 2x2 STST and 6MWT protocols together, for example, lasted for at least 2 hours and had to be completed within the same day. Reasonable allowance was also made for unexpected factors such as the inability of a participant to complete all of the tests or the withdrawal of consent following inclusion in the study.

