STST will be conducted in a quiet room, in a similar environment in each center. The test will be performed using a vertically adjustable chair without arm-rests to account for the variability in leg length in participants. The chair height will be set to ensure 90° of knee flexion during the test. The test will be explained using standardized information in all Centers, and subjects will be allowed to perform several sit-to-stand movements before the test to familiarize themselves with the procedure. Beginning position will be subjects seated, with a 90° knee flexion angle and arms across the chest [10]. Explanations will be: « This test aims to assess your exercise capacity. The aim is to stand up as many times as possible in 1-minute. The number of repetitions that you will perform will be recorded. I will let you know when there will be only 15 seconds left. You are allowed to stop or rest during the test ». Resting periods will be authorized but the clock will not be stopped if the subject stops.

*6MWT*

The 6MWT will be conducted according to the ATS/ERS guidelines [2]. The test conditions will be standardized in each Center. The subjects will be asked to walk the greatest distance they can reach in 6-minutes. The test will take place in a 30-meters corridor. A visible mark will be placed at both extremities. Standardized information will be given each minute according to guidelines « Keep going» as well as the time remaining before the end of the test. Resting periods will be authorized but the clock will not be stopped if the subject stops.

*Rest periods*

A 30-minutes rest period will take place between the first and the second row of field tests. Similarly, a 30-minutes rest period will also take place between each different test. The rest period will take place in a quiet environment. The subjects will be asked to stay calm, not perform any exercise, and a cold drink (water but not sweetened drink) will be proposed.

Study design:

Children with CF meeting the inclusion criteria

*24-hour pre-inclusion delay*

Signed informed consent

Data collection

Randomization

6MWT

STST

STST

6MWT

Data collection

This study will be conducted according to the protocol and the legislation for clinical trial conduction.

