**Stopping criteria**

All the investigators of this study are habituated to the conduction of such field tests and will consistently be watching over the children included in each Center. No side effects will be expected to occur.

The study procedure will be stopped if any exclusion criteria appears or upon request of the children.

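### Excluding enrolled children who cannot complete the procedure conditions the primary correlation on completing the tests under validation, and may selectively lose less fit or younger children

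*Protocol*

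**What the plan says.** The protocol separates non-inclusion criteria, applied before entry, from exclusion criteria. The first exclusion criterion is "Unability to complete the study procedure". Under Stopping criteria: "The study procedure will be stopped if any exclusion criteria appears or upon request of the children". The rule therefore operates on children who have consented and started testing.

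Sample size estimation states that "36 participants were necessary to detect a correlation coefficient of 0.45 between the STST and 6MWT performances"; power is set at 80% and alpha at 0.05. It continues: "The final sample size aimed for was 40", citing attrition of about 10% and the length of the session (at least 2 hours, in one day). It adds: "Reasonable allowance was also made for unexpected factors such as the inability of a participant to complete all of the tests", and names withdrawal of consent as well.

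Under Study procedures, each test is done once for habituation and then a second time in randomized order. Children are told before the STST: "You are allowed to stop or rest during the test". Rests are permitted in both tests while the clock keeps running.

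The paragraph on external validity expects that the STST "could easily be used in young children with CF". One secondary objective concerns children aged 6 to 10.

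**The concern.** Whether a child can finish four exercise tests in a day is a result of the testing, not a baseline characteristic. Using it to define who stays in the study makes the analysed sample depend on the performance being measured. If those who drop out tend to have low capacity, the spread of both test results narrows at the bottom and the correlation between them is attenuated. In a study sized at about 80% power for r = 0.45, with 36 children, there is little room for that.

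Inflating 36 to 40 replaces the lost head-count but does not undo a selective loss. Some of the loss is also avoidable. A child who rests or stops early within a test has a legitimate low score, and a child who fails at a later step may already have scores on both tests.

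Finally, an expectation of easy use in young children is less well supported if children who could not finish leave the study and nothing requires them to be described.

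**Working it through.** **Inputs from the protocol (Sample size estimation):** r = 0.45; 36 analysed; 80% power; alpha 0.05 (sidedness not stated, two-sided assumed); about 10% attrition; 40 recruited.

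**1. The plan's own figures.** With the Fisher z transformation, n = ((z_alpha + z_power) / atanh(r))² + 3. Here atanh(0.45) = 0.4847, so n = ((1.960 + 0.842) / 0.4847)² + 3 = 36.4. This agrees with 36 to within rounding. A one-sided test would give 30, so two-sided is the reading that fits. Power at n = 36 is Φ(0.4847 × √33 − 1.960) = Φ(0.824) = 79.5%. Recruitment: 36 / 0.9 = 40. Both stated figures are reproduced.

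**2. Model for selective loss (assumption).** Each test score = √0.45 × g + √0.55 × independent error, with g the latent capacity and everything standard normal, so the correlation among all enrolled children is 0.45. Ten per cent are lost, by different mechanisms. r is recomputed in those who remain (simulation, millions of draws), and power is Φ(atanh(r) × √33 − 1.960) with 36 analysed.

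| How the 10% are lost | r in completers | Power, n = 36 |
|---|---|---|
| Unrelated to capacity | 0.45 | about 80% |
| Odds of non-completion ×2 per SD lower g | 0.44 | 78% |
| ×3 per SD | 0.43 | 75% |
| ×5 per SD | 0.42 | 72% |
| Exactly the lowest 10% on one test | 0.39 | 66% |
| Exactly the lowest 10% on g | 0.37 | 60% |
| Exactly the lowest 10% on the sum of both tests | 0.31 | 44% |

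The odds ratios are assumed; the documents supply none. The last three rows are perfect truncation, with no chance element and no loss for other reasons.

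**3. Are non-completers' scores actually lost?** The exclusion criterion does not say that collected data are discarded, and Stopping criteria says only that the procedure ends. But the allowance in the sample size section makes sense only if a child unable to complete all tests does not count toward the 36. Read together, the two sections leave such children out of the primary correlation.

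**The case against.** The strongest reply is that nothing in the protocol says non-completers are the least fit. Attrition is attributed to a long session, with consent withdrawal as a further reason. Entry criteria already screen out contra-indications and require clinical stability. Because rests are allowed, a slow child normally finishes with a low score and stays in, which protects the lower end of the range. All of this stands. A reader might infer that the rule removes the weakest tenth and that r will be seen as 0.31 to 0.39. The documents do not support that as the expected result; it is the far end of the range.

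A reader might also infer that the rule flatters the validity result. Under the model above it does the opposite: the correlation is lowered, against the study hypothesis. The cost is lost power and an attenuated estimate, not a false positive. Nor is there a feasibility claim to inflate, since feasibility is neither an objective nor an endpoint and the remark on young children is an expectation.

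It can also be said that the handling of partial data belongs in an analysis plan that is not shown. That would answer the point if the protocol were silent. It is not: it makes non-completion an exclusion criterion and counts it as attrition.

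Last, the first run is defined as habituation, so treating first-run scores as primary data would go against the design. That is correct and limits the fix.

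**Conclusion.** The point holds as a design weakness of moderate importance. The protocol conditions its primary correlation on completing the tests being validated, and this may selectively lose less fit or younger children. How much it matters depends on something the documents do not report, namely who fails to complete. With 10% lost and a true r of 0.45, an association of odds ratio 2 to 5 per SD of capacity costs about 2 to 8 percentage points of power (79.5% to between 78% and 72%). The worst case costs about 13 to 35 points (to between 66% and 44%). Random loss costs nothing beyond the head-count already allowed for. These figures rest on a normal one-factor model and a two-sided test.

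Confidence is high that the rule exists and acts after enrolment, and low on the size of its effect. The weakening of the ease-of-use expectation is real but secondary.

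**What to change.** Reword the exclusion criterion so that it ends testing for that child but does not remove data already collected; the grounds for stopping are left as they are. Then state:

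- **Primary analysis:** every enrolled child with a scored second-run STST and a scored second-run 6MWT, even if other parts of the procedure are missing. A test with rests or an early stop is scored as the count or distance reached.
- **Sensitivity analysis:** use the first-run score where the second run is missing.
- **Reporting:** for each test, the number of children who could not complete it, with age and reason.

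This needs protocol and analysis wording only, with no new measurements and no change to 36 or 40. The small downside is that first-run scores carry a learning effect, which is why they are confined to the sensitivity analysis. Children with no score on one of the tests still cannot contribute to the correlation, so selective loss is reduced rather than removed; the reporting item lets readers judge what remains.

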**Sample size estimation**

The sample size estimation showed that 36 participants were necessary to detect a correlation coefficient of 0.45 between the STST and 6MWT performances, with 80% power and an alpha level of 0.05. The final sample size aimed for was 40 since it was estimated that there would be an attrition rate of approximately 10%, based on experience in using these clinical tests with children: the 2x2 STST and 6MWT protocols together, for example, lasted for at least 2 hours and had to be completed within the same day. Reasonable allowance was also made for unexpected factors such as the inability of a participant to complete all of the tests or the withdrawal of consent following inclusion in the study.

**Randomization procedure**

The randomization sequence will be computer-generated by a person not involved in the study using a random block size on a 1:1 ratio and will be sent to each of the CF Centers at the beginning of the study by the principal investigator (YC).

**Study procedures**

Data collection

After the reception of the signed informed consent, the investigators will collect the age, gender, weight, height, BMI, number of exacerbations and hospitalizations in the last year and the results of the latest pulmonary function testing (FVC, FEV1, PEF).

Respiratory muscle strength will then be measured. MIP and MEP will be measured using a unidirectional valve electronical manometer MicroRPM PUMA© according to the American Thoracic Society latest guidelines [4]. Each measure will be conducted three times and the best value will be recorded. The data collection of respiratory muscle strength will be the same in each CF Center.

QS will be measured using a hand-held dynamometer. Computerized dynamometric assessment of the quadriceps muscle is reproducible in adolescents with CF [5]. However, due to financial and technical limitations, we will be using a hand-held dynamometer. QS will be measured using the MicroFET2© that has shown reliability in both healthy adolescents and patients with COPD [6, 7]. High inter-rater reliability has been proven to ensure reproducible values between each CF Center. Standardized measures will be conducted using a belt stabilization to avoid measures errors [6, 7]. Each child will be seated with the legs pending, hip and knee flexed at 90° and the dynamometer will be placed on the anterior face of the dominant leg. 5 repetitions (lasting from 4 to 6 seconds) will be conducted and the best of the last 3 values will be recorded for the analysis. A rest period of 30 to 60 seconds will be respected between each measure [6].

All the children will complete the CFQ-R (Cystic Fibrosis Questionnaire). The French version of this scale has been validated [8]. 3 different questionnaires have been described: for children from 6 to 11 years, from 12 to 13 years and older than 14 years. All the procedures for the children and the investigators are precisely described within the scale completion document. The investigators will only have to help the children from 6 to 11 years by reading the questions and give examples whenever required. All the questions will be verbally answered by the children and answers will be reported on the questionnaire by the investigators. Two combinations are described for the different questions: « Très vrai / Vrai dans l’ensemble / Un peu vrai / Pas du tout vrai » and « Toujours / Souvent / parfois / Jamais ». A parental version of the questionnaire will be completed by the parents for the children younger than 14. Older children will complete the questionnaire on their own. The questionnaire will be filled in a quiet room.

Field tests realization:

Both field tests will be conducted twice. After the primary data collection, each test will be conducted once to account for the learning effect. The results of these first tests will not be transmitted to the children.

Both tests will then take place a second time. A 30-minute rest period will last between the habituation tests and the first field test and between both tests. The order of these tests will be randomized. HR, RR, BP, SpO2, dyspnea and leg fatigue will be measured before and after each test.

*STST*

STST will be conducted in a quiet room, in a similar environment in each center. The test will be performed using a vertically adjustable chair without arm-rests to account for the variability in leg length in participants. The chair height will be set to ensure 90° of knee flexion during the test. The test will be explained using standardized information in all Centers, and subjects will be allowed to perform several sit-to-stand movements before the test to familiarize themselves with the procedure. Beginning position will be subjects seated, with a 90° knee flexion angle and arms across the chest [10]. Explanations will be: « This test aims to assess your exercise capacity. The aim is to stand up as many times as possible in 1-minute. The number of repetitions that you will perform will be recorded. I will let you know when there will be only 15 seconds left. You are allowed to stop or rest during the test ». Resting periods will be authorized but the clock will not be stopped if the subject stops.

*6MWT*

The 6MWT will be conducted according to the ATS/ERS guidelines [2]. The test conditions will be standardized in each Center. The subjects will be asked to walk the greatest distance they can reach in 6-minutes. The test will take place in a 30-meters corridor. A visible mark will be placed at both extremities. Standardized information will be given each minute according to guidelines « Keep going» as well as the time remaining before the end of the test. Resting periods will be authorized but the clock will not be stopped if the subject stops.

*Rest periods*

A 30-minutes rest period will take place between the first and the second row of field tests. Similarly, a 30-minutes rest period will also take place between each different test. The rest period will take place in a quiet environment. The subjects will be asked to stay calm, not perform any exercise, and a cold drink (water but not sweetened drink) will be proposed.

Study design:

Children with CF meeting the inclusion criteria

*24-hour pre-inclusion delay*

Signed informed consent

Data collection

Randomization

6MWT

STST

STST

6MWT

Data collection

This study will be conducted according to the protocol and the legislation for clinical trial conduction.

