**Analysis**

Statistical analysis will be conducted with GraphPad Prism 5. The distribution of the variables will be evaluated with the Shapiro-Wilk test and parametric or non-parametric tests will be utilized accordingly. Pearson and Spearman tests will be conducted to assess the correlations between the different outcomes.

The significance level will be set at p<0.05.

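### Readings are taken before every test, but the protocol does not define the response or adjust for starting level, so the STST versus 6MWT comparison may lose precision

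*Protocol*

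**What the plan says.** Under Study procedures (field tests), the protocol states that "HR, RR, BP, SpO2, dyspnea and leg fatigue will be measured before and after each test". Each child performs each test twice, so there are four pairs of readings.

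Two secondary objectives under Specifical objectives use them. One concerns the two tests: "Compare the cardio-respiratory responses between both different tests (HR, RR, SpO2, BP, dyspnea and leg fatigue". The other concerns the two runs of one test: "Compare the cardio-respiratory responses between both similar tests (HR, RR, SpO2, BP, dyspnea and leg fatigue".

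The Analysis section says: "The distribution of the variables will be evaluated with the Shapiro-Wilk test and parametric or non-parametric tests will be utilized accordingly". It adds that "Pearson and Spearman tests will be conducted to assess the correlations between the different outcomes" and that "The significance level will be set at p<0.05". No section says what quantity a response is, or how the pre-test reading enters a comparison.

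Two design facts matter. The order of STST and 6MWT is randomised. The order of the two runs is fixed: the habituation run comes first, with a 30-minute rest before the second round.

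**The concern.** The section on the validity of the study presents lower cardio-respiratory responses, dyspnea and fatigue as a possible advantage of the STST, so the comparison with the 6MWT matters to the conclusions. With the methods named, the analyst has two natural choices. The post-test value ignores where the child started. The raw change uses the starting value but fixes its slope at exactly 1 and carries the full noise of the pre-test reading. Regression on the pre-test difference estimates the slope from the data and, apart from the small cost of estimating it, is never less precise than either.

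At stake is precision in a small sample. The choice between post-test value and change is also left open for six variables, and the two can give different answers from the same children.

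**Working it through.** **The plan's own figure.** The Sample size estimation section reads: "36 participants were necessary to detect a correlation coefficient of 0.45 between the STST and 6MWT performances, with 80% power and an alpha level of"; the level given there is 0.05. Fisher's z, two-sided, gives n = ((1.960 + 0.842) / atanh(0.45))² + 3 = 36.4. That rounds up to 37, or is 36 with the small bias term r/(2(n − 1)), so the stated 36 is reproduced. With 10% attrition, 36 / 0.90 = 40, as stated. This calculation sizes the STST–6MWT correlation only and does not depend on the present point.

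**Inputs for the comparison.** n = 36 is from the protocol. The protocol gives no SDs or correlations for the six variables, so rho and k below are assumptions shown over a range.

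**Definitions.** For each child, D is the STST minus 6MWT difference in post-test readings and B is the same difference in pre-test readings. Then rho = corr(D, B) and k = SD(B)/SD(D). Set Var(D) = 1.

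- Post-test value only: variance 1.
- Raw change (D − B): variance 1 + k² − 2·rho·k.
- Adjusted (D regressed on B): variance 1 − rho².

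Raw change minus adjusted is (1 + k² − 2·rho·k) − (1 − rho²) = (k − rho)². The two are therefore equal when k = rho, and change is worse otherwise. Change beats post-only when k < 2·rho.

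| rho | Post-only | Adjusted | Change, k = 0.5 | Change, k = 0.7 | Change, k = 1 |
|---|---|---|---|---|---|
| 0.2 | 1 | 0.96 | 1.05 | 1.21 | 1.60 |
| 0.3 | 1 | 0.91 | 0.95 | 1.07 | 1.40 |
| 0.5 | 1 | 0.75 | 0.75 | 0.79 | 1.00 |

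**In numbers of children.** Adjusted analysis of 36 children is worth 36/0.96 = 37.5, 36/0.91 = 39.6 and 36/0.75 = 48 children analysed post-only. Raw change at k = 1 is worth 36/1.60 = 22.5, 36/1.40 = 25.7 and 36.

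**Cost of estimating the slope.** At n = 36 this multiplies the adjusted variance by about 35/34 = 1.03, giving 0.99, 0.94 and 0.77. At rho = 0.2 the gain over post-only has almost gone.

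**Power.** A post-only paired t-test on 36 children has 80% power for a difference of 0.48 SD of D. At that difference, adjustment gives about 82%, 84% and 90% for rho 0.2, 0.3 and 0.5, slightly optimistic because the 1.03 factor is left out. Raw change with k = 1 gives about 60%, 66% and 80%.

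**The case against.** The strongest reply is that choosing between post-test value, change and covariate adjustment for a secondary outcome is ordinary SAP content, and a SAP may exist. That stands as far as detail goes. But the protocol has an Analysis section that names the kind of method, and none of those named adjusts for the starting level.

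A reader might infer that the protocol discards the pre-test readings. The text does not support this. It is silent on their use, and with readings before and after each test, *response* can naturally mean the change, which does use them.

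The gain can also be small. At k = 0.5 and rho = 0.5 raw change and adjustment have the same variance, and at rho = 0.3 they differ only as 0.95 to 0.91. The large losses for raw change arise when k is well above rho.

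A reader might further infer that the run 1 versus run 2 comparison is biased and that adjustment would cure it. Run order is fixed, so starting levels may differ systematically. For a starting difference d and slope b, post-only departs from the adjusted estimate by b·d and change by (b − 1)·d; with an assumed 5 bpm and slope 0.5 that is +2.5 and −2.5 bpm. These departures count as bias only if the adjusted quantity is taken as the truth. In a fixed-order comparison that is debatable, and noise in the pre-test reading attenuates the slope. The protocol also standardises a quiet rest before the second round and between different tests.

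Finally, partialling the pre-test reading out of the performance–response correlations would change the question that the objectives set.

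**Conclusion.** The point holds as one of definition and precision in the secondary STST versus 6MWT comparison. The response is undefined, and the methods named lead to the post-test value or the raw change when data already scheduled would support a usually more precise analysis. Relative to post-only, the gain in variance is about 4% at rho 0.2, 9% at 0.3 and 25% at 0.5, less about 3% for estimating the slope. Relative to raw change it is (k − rho)², from nothing to 0.64 over the values shown.

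The conclusion rests on assumed rho and k, and on randomised order balancing starting levels in expectation. The latter requires that whatever carries over the 30-minute rest is the same after either test. The documents do not support a claim of bias in this comparison, a demonstrated bias in the run comparison, or any effect on the primary correlation or the sample size.

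**What to change.** In the Analysis section:

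- Define the response for each of the six variables.
- STST versus 6MWT, for HR, RR, BP and SpO2: regress the within-child difference in post-test readings on the within-child difference in pre-test readings, with a term for randomised test order. Report the adjusted mean difference (at zero pre-test difference, averaged over the two orders) with a 95% CI.
- STST versus 6MWT, for dyspnea and leg fatigue: use a rank-based analysis with a matching effect measure, for example a Hodges–Lehmann estimate of the within-child difference with its CI. State whether it is applied to the post-test score or the change. An adjusted mean difference does not belong with a rank method.
- Run 1 versus run 2: report the pre-test readings and the change alongside the adjusted result, and do not claim that adjustment removes bias.
- Leave the performance–response correlations as stated.

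The cost is wording, plus one or two extra model terms per comparison. No new measurement or participant is needed. The sponsor should confirm that the software named in the Analysis section can fit the model. If rho turns out low, little is gained.
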